## Abstract

**Introduction:**

Action Observation Treatment (AOT) and Motor Imagery (MI) represent very promising cognitive strategies in neuro-rehabilitation. This study aims to compare the effectiveness of the two cognitive strategies, taken alone or combined, in Parkinson's disease patients.

**Material and methods:**

This study is designed as a prospective randomized controlled trial, with four arms. We estimated a sample size of 64 patients (16 in each treatment group) to be able to detect an effect size of *F* = 0.4 with a statistical significance of 0.05. Primary outcomes will be functional gains in the FIM and UPDRS scales. Secondary outcome measure will be functional gain as revealed by kinematic parameters measured at Gait Analysis.

**Discussion:**

The results of this trial will provide insights into the use of AOT and MI, taken alone or combined, in the rehabilitation of Parkinson's disease patients.

**Ethics and dissemination:**

The study protocol was approved by the Ethics Committee of the Don Gnocchi Foundation. The study will be conducted in accordance with the 1996 World Medical Association guidelines and according to good clinical practice. The study has been registered on clinicaltrial.gov under the following code: AOTPRFDG. Dissemination will include both submission of the study to peer-reviewed journals and discussion of the study protocol at conferences.

## Introduction

There is increasing evidence in neuroscience of the existence of a mirror mechanism directly matching observed actions on the neural substrates sub-serving their execution (1, 2). It has been forwarded that this mechanism allows individuals to understand other people's actions on an experiential basis, because of the re-enactment of the motor representations also involved in the actual execution of the observed actions. At neural level this mechanism may be grounded on the existence of mirror neurons first described in monkey pre-motor cortex (3, 4). These neurons discharge during the execution of goal directed actions, as well as during the observation of those same actions or related ones. In more general terms, experimental evidence supports the notion that the neural substrates involved in action execution are recruited whenever actions are re-enacted, like for example in motor imagery or even during dreams with motor content (5). In recent times, it has been proposed an action re-enactment also during the processing of action related language, that is verbs typically describing an action (6, 7). The notion of action re-enactment, based on visual stimuli or on an internal mental rehearse of an action in the absence of overt movements, has recently inspired the use of the action-observation treatment and the motor imagery practice as neurocognitive rehabilitation strategies.

In action observation, patients are shown a video clip representing a goal-directed action (e.g., grasping an object). Subsequently, after observing this video, the patient is asked to repeat the action. So far, treatment with AOT has been shown to be effective in a variety of different pathologies such as ischemic stroke (both chronic and subacute; both on walking and upper limb function) (8–10), cerebral palsy (11–13); Parkinson's disease (14, 15) and also in orthopedic patients with hip fractures (16).

Jeannerod defines motor imagery as the ability to “mentally rehearse simple or complex motor acts that are not accompanied by overt body movements” (17). From a cognitive point of view, it is a perceptive process that occurs in absence of external stimuli. Motor imagery was first studied in cognitive psychology and neuropsychology (18), then applied to sport (19, 20) in order to improve the physical performance of athletes and has recently been applied in rehabilitation medicine to improve the physical recovery of patients with neurological disabilities (21–23). Motor imagery is associated with the activation of several cortical areas that are also involved in action observation and execution (24–27). In particular, the areas that are activated by motor imagery are the ventral premotor cortex (PMv), inferior frontal gyrus (IFG), inferior parietal lobule (IPL), supramarginal gyrus (SMG), sensorimotor area (SMA), cerebellum and basal ganglia (28, 29).

Parkinson's disease is the second most common neurodegenerative disease. In the coming decades, the prevalence of the disease is expected to increase, partly due to the increasing average age of the population. This trend will consequently lead to an increase in the costs related to the medical and social management of the disease, most of which are attributable to the more advanced stages of the disease and directly related to disability, increased care burden and therapeutic complications (30, 31).

Recently, several studies have focused on the applicability of action observation treatment (15, 32) and motor imagery (33, 34) in the rehabilitation of patients with Parkinson's disease. While AOT appears to be effective in improving motor performance, the effectiveness of Motor Imagery is not yet well defined also due to the presence of contrasting data in the literature. This may also be linked to the fact that the subject's ability to imagine depends on many factors (one in particular is the anatomical integrity of the cortical structures connected to this ability), but also to the fact that this ability is poorly investigable (35) and recently a systematic review has emphasized that some areas also involved in Parkinson's disease, if affected, can reduce the capacity to imagine actions (36).

Based on those evidence, we came up with the concept of evaluating the effectiveness of these two cognitive strategies, motor imagery and action observation, in the rehabilitation of Parkinson's disease patients. Based on the ongoing debate and the evidence that action observation is more effective than motor imagery in learning a novel, complex motor task in healthy individuals (37), the first point we want to assess is whether Motor Imagery and action observation are similarly effective, when taken alone, in Parkinson's disease patients. Second, this study aims to assess whether the combination of the two is more effective than the individual treatments. In fact, recent evidence show that motor performance is improved when motor imagery is associated with synchronous action observation of the imagined actions (38).

## Methods and analysis

### Study design

The aim of the study is to evaluate the efficacy of action-observation (AOT) and motor imagery (MI) treatment on the improvement of function and motility in patients with Parkinson's disease with a disease stage II or III according to Hoehn and Yahr. The study was approved by the ethical committee of the IRCCS Don Gnocchi, Milan. The study has been registered to clinicaltrial.gov with the Study ID number: AOTPRFDG. All procedure will be conducted according to the World Medical Association (WMA - 1996) and, when applicable, according to the procedure recommended by the Italian Association of Psychology (AIP). Before starting the study, each patient will be asked for written and verbal informed consent. Motor and functional assessments will be performed at T0 (baseline assessment)–T1 (4 weeks later, at discharge) and T2 (2 months after discharge, as outpatients).

### Study sample and inclusion/exclusion criteria

Patients will be selected from those referred to the intensive rehabilitation unit and Parkinson's service of Don Carlo Gnocchi Foundation, Santa Maria ai Servi Center, Parma. In this setting, patients, aged between 55 and 75 years and with a disease stage II or III according to Hoehn and Yahr, will be enrolled. Exclusion criteria will be the presence of aphasia (evaluated with the token test), hemispatial neglect (assessed with the line bisection test of the Behavioral Inattention Test battery), global cognitive impairment (assessed with the Mini Mental State examination—MMSE, score <24/30), motor apraxia (assessed with the De Renzi gesture imitation test), and major depression (assessed by the Beck Depression Inventory II).

### Randomization

Each patient will then be associated with a randomly generated numerical code and randomly assigned to one of four groups: Motor Imagery + Conventional Treatment; AOT + Conventional Treatment, AOT + Motor Imagery + Conventional Treatment and Control Group + Conventional Treatment. The randomization will be carried out by an independent researcher who will be not involved further in the study.

### Sample size

The sample size has been defined by the achievement of outcome measures. In this study, our outcome measures are an improvement in motor functions and kinematic parameters of patients suffering from Parkinson's disease, as revealed by means of functional scales (FIM, UPDRS) and gait analysis. In order to detect an effect size of *F* = 0.4 (medium to large effect size, according to Cohen, 1988) (39) with 80% power and 0.05 alpha in a mixed subjects design (4 groups and 3 time points), G^*^Power suggests that a total sample size of 64 participants (16 participants for each group) should be enrolled. We plan a sample size of *N* = 80 (*N* for each group = 20) that will be more than adequate to control for a potential participants' drop out. Furthermore, this sample size will be adequate to ensure that data can be interpreted separately, for each group.

### Blinding

Patients in each group will be instructed in the specific task for that group. An experienced, blinded researcher will administer functional scales to enrolled subjects at T0, T1, and T2. Another experienced blinded operator will perform the gait analysis at T0, T1, and T2.

### Treatment protocol

Enrolled patients will undergo a standard neurological and physiatric evaluation, a neuropsychological assessment, and gait analysis. Function and independence will be quantified with the FIM scale and UPDRS. In addition, a visual and kinesthetic imagination scale (MIQ-R) will be delivered to each patient enrolled. The patients then will undergo a 4-week inpatient treatment (excluding weekends), at the end of which the functional assessment (FIM scale and UPRDS) as well Gait Analysis will be repeated. The euro Quality of Live (eQoL) questionnaire will be administered to each subject on admission and at discharge. During hospitalization, at a fixed day time, the patient will undergo a conventional rehabilitation treatment administered by a physiotherapist different from the one involved in the study. All treatments will be carried out in ON phase patients. Study protocol is summarized in Figure 1. In the follow-up evaluation at T2 participants will be assessed as outpatients.

**Figure 1 F1:**
[figure not shown]
Flow chart of the study protocol.

### Conventional treatment

Conventional treatment will consist of 10 min of active kinesis with limb and trunk mobilization exercises; 5 min of ischio-crural, adductor, hip flexor and plantar flexor foot muscles stretching; 10 min of postural spine extension exercises; 5 min of gait training to improve gait phases and dynamic balance and 5 min of coordination exercises.

### Action-observation treatment

Patient will undergo AOT according to the procedure described in a comprehensive review in the field (40). During a typical AOT rehabilitation session, patients train one single daily life action. Actions to be trained are chosen among those most frequently carried out in everyday life. An AOT rehabilitation session consists of an observation phase and an execution phase. During the observation phase, the patient sits in front of a computer screen and has to observe a videoclip, showing the execution of a specific action. The presented action can be divided into four motor acts, each lasting 3 min, for a total of 12 min. Motor acts are defined as the different action segments into which the action can be divided. For example, washing one's hands can be divided into the following motor acts: (I) applying soap on wet hands; (II) scrubbing hands for a few seconds; (III) rinsing hands under running water; (IV) drying them with a towel. Each motor act is performed by both an actor and an actress and is presented from different perspectives in order to catch the attention of the patient. After observing a single motor act, the patient moves to the action execution phase where he/she is required to perform the same action, at the best of his/her abilities, for 2 min. Every object present in the video clip is provided at hand to the patient during this phase. Indeed, it is well known that objects can recruit the motor representation of an action, thus further enhancing the re-organization of the motor system (41–43).

### Motor imagery

The proposed motor imagery activity will be carried out by showing the same videos used in AOT. In this group each video will be shown to the patient just for a few seconds. Following this short observation period, the patient will be asked to imagine himself/herself performing the observed action for 3 min (the same time devoted to observation in the AOT group). Following the imagery task the patient will be asked to reproduce the imagined action for 2 min as patient in the AOT group. Every now and then, the physiotherapist will monitor the imagery activity by asking the patient at what time point of the action he/she is.

### Action observation treatment + motor imagery

This group will undergo AOT as already described. After observing each motor act, patients in this group will be asked to imagine the observed model for 3 min in first person perspective (as if he/she should be performing the seen motor act). At the end of the motor imagery, patients in this group will be asked to perform the observed and imagined motor sequence at the best of their ability for 2 min. As usual, the physiotherapist will help patients to pay attention to the task and sustain their motivation.

### Control treatment

For the control group, twenty videos will be prepared representing situations with no specific motor content. Also in this case videos will consist of 43-min parts with a total duration of 12 min. The patient will be asked to watch the videos. After observing this motorically neutral videoclips, the patients will be requested verbally to perform one of the motor activities actually executed by patients enrolled in the AOT or MI groups. In other words, the execution phase in this group will overlap that of patients in the other study groups. In this manner patients in this group will spend the same amount of time in the observation phase, as well as in the execution phase, as patients in the study groups.

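### The control arm's stated time match cannot be true of all three active arms, and the combined arm's 12 extra minutes per session limit what an advantage there can show

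*Protocol article*

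**What the plan says.** The Control treatment section of the protocol article describes an attention control. For it, "twenty videos will be prepared representing situations with no specific motor content", with 12 min of viewing per session. Control patients then carry out the same motor activities as the others: "the execution phase in this group will overlap that of patients in the other study groups". The section concludes that control patients "will spend the same amount of time in the observation phase, as well as in the execution phase, as patients in the study groups". No exception is made for the combined arm.

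The active arms are timed in their own sections:

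- **AOT** (Action-observation treatment): four motor acts of 3 min of observation each, with 2 min of execution after each act.
- **MI** (Motor imagery): "In this group each video will be shown to the patient just for a few seconds". The patient then spends the time imagining, "performing the observed action for 3 min (the same time devoted to observation in the AOT group", and executes for 2 min as in AOT.
- **AOT+MI** (Action observation treatment + motor imagery): "This group will undergo AOT as already described". Imagery is then added: "After observing each motor act, patients in this group will be asked to imagine the observed model for 3 min". Execution of 2 min follows.

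The Introduction gives the second aim as whether the combination does better than either treatment alone, and the Discussion repeats it. The Discussion also sets out a comparison of the cognitive strategies with conventional rehabilitation.

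**The concern.** The neutral-video control is there to equalise time and attention, so that a difference from control can be put down to the content of the treatment. The closing sentence of Control treatment presents that equality as a property of the design. The timings in the neighbouring sections do not bear it out for every active arm.

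The combined arm keeps all of the AOT observation and adds imagery on top. Nothing is shortened in that arm, and no filler time is added to the other three. Extra time therefore goes entirely with assignment to AOT+MI, and the planned mixed ANOVA cannot separate the two. A reader who relied on the sentence could credit an AOT+MI advantage to the content of the combination when added practice time explains it equally well. This affects the contrast with control and also the contrasts with AOT and MI alone, which carry the second aim.

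**Working it through.** **The plan's own figure.** AOT observation is 4 acts × 3 min = 12 min per session. This agrees with the totals stated for AOT and for the control video.

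**Inputs.** Observation, imagery and execution times come from the four treatment sections. Two points are inferred:

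- The MI cycle is taken to be repeated for each of the four acts. The parenthesis equating imagery time with AOT observation time implies this but does not state it.
- The short MI clip has no stated length; 5 to 15 s is assumed here.

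**Time per session, in minutes**

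| Arm | Viewing | Imagery | Viewing + imagery | Execution | Session |
|---|---|---|---|---|---|
| Control | 12 | 0 | 12 | 8 | 20 |
| AOT | 4 × 3 = 12 | 0 | 12 | 4 × 2 = 8 | 20 |
| MI | 4 × (5 to 15 s) = 0.3 to 1.0 | 4 × 3 = 12 | 12.3 to 13.0 | 4 × 2 = 8 | 20.3 to 21.0 |
| AOT+MI | 4 × 3 = 12 | 4 × 3 = 12 | 4 × (3 + 3) = 24 | 4 × 2 = 8 | 32 |

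Control execution is set at 8 min because its section says it overlaps that of the other groups.

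**Testing the matching sentence**

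1. *Imagery counts as time before execution.* Control 12 against AOT 12: matched. Control 12 against MI about 12: matched, apart from the short clips. Control 12 against AOT+MI 24: not matched.
2. *Only video viewing counts.* Control 12 against AOT 12 and AOT+MI 12: matched. Control 12 against MI 0.3 to 1.0: not matched.

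Each reading fails for one active arm, and it is a different arm each time.

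**The time difference, which does not depend on the reading**

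- AOT+MI minus control, and AOT+MI minus AOT: 32 − 20 = 12 min per session. Viewing plus imagery is doubled (24/12 = 2) and the study session is 60% longer (32/20 = 1.6).
- AOT+MI minus MI: 32 − 21.0 = 11.0 to 32 − 20.3 = 11.7 min, so about 12.

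**Over the course, for illustration only.** With one session per weekday for 4 weeks, 4 × 5 = 20 sessions, the excess over control or AOT is 20 × 12 = 240 min (4 h). This frequency fits the twenty control videos and the weekday inpatient stay, but the article does not state it.

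**The case against.** The strongest reply is literal. The sentence names two phases, observation and execution. The AOT section defines observation as watching a clip on a screen, and the AOT+MI section places imagery after observation and before execution. On those terms AOT+MI has 12 min of observation and 8 min of execution, exactly as control does. This stands. A reader might infer that the match is simply false for the combined arm and holds only for the single-treatment arms; the documents do not support that. What the literal reading cannot do is rescue the sentence, because MI then fails.

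It can also be said that the sentence was meant only for the AOT and MI arms, which are named shortly before it. That may be the intention. But the sentence itself speaks of the study groups without limit, and the one before it refers to all the other groups. If the narrower meaning was intended, the remedy is to write it.

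A third reply is that nothing is hidden: the added imagery is stated in the preceding section, and extra time is inherent when a full-dose component is added. That too stands. One might infer that the combined arm is badly designed or that the second aim cannot be answered. Neither follows, because whether adding the second component helps is a proper question and the design answers it. The article also nowhere says that an advantage will be credited to combining net of time.

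Finally, a reader might take the statement that "the physiotherapist will help patients to pay attention to the task and sustain their motivation" as support peculiar to AOT+MI. The text introduces it as usual practice, and the Motor imagery section also has the physiotherapist monitoring patients. Any difference in contact would lie in its duration, not its presence.

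**Conclusion.** The sentence is wrong as written; the severity is minor. It states a property that the design has for two of the three active arms at a time, but never for all three under one definition. Execution time is matched.

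What matters for interpretation is the 12 min of additional study task per session in AOT+MI relative to control and AOT, and about 12 min relative to MI. An AOT+MI advantage in any of these contrasts cannot be separated from that time. AOT against control is time-matched as claimed. MI against control, and AOT against MI, are approximately matched.

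The 24 against 12 min and the 32 against 20 min come directly from the stated timings. The MI figures rest on the per-act cycle and the assumed clip length, and the 240 min rests on an assumed 20 sessions. The conclusion needs none of these assumptions for AOT+MI against control or AOT.

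**What to change.** In Control treatment, replace the closing sentence with one to this effect: control is matched to the AOT and MI arms on total time before execution (12 min of video against 12 min of observation or imagery) and on execution time (8 min); the AOT+MI arm has 12 min more per session. For this to be exact, the Motor imagery section should say that its cycle is repeated for each motor act, if that is the intention.

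Add one statement of interpretation: contrasts involving AOT+MI estimate the effect of adding the second full-dose component, including its extra time, and an advantage will not be attributed to combining as such.

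The cost is a few sentences. Arms, analysis, alpha and sample size are untouched. The downside is that the second aim supports a narrower claim.

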### Pre-clinical and clinical evaluation

The Clinical evaluation of patients will take place in the intensive rehabilitation department of the Don Carlo Gnocchi Foundation, Santa Maria ai Servi Center, Parma.

### Demographic and clinical characteristics

The patients will be classified according to Hoehn and Yahr scale. This classification allows the degree of disability to be assessed on a scale of I to V. Patients classified from stage I to stage III are defined as mildly disabled, while those in stage IV or V are defined as severely disabled (44). The HY scale is widely used in clinical settings to classify the level of disability of Parkinson's patients because it is simple, easily applicable and reliable. It also has a good correlation with the UPDRS scale (45). The anagraphic (age and sex) and clinical characteristics of the subjects will be assessed at T0 (baseline) in all groups to evaluate their homogeneity.

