### Outcome measures

Primary outcome measures will be score changes in two functional scales: FIM and UPDRS. Secondary outcome measures will be changes in kinematic parameters as revealed by gait analysis.

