### Statistical analysis

The statistical analysis of the data will be carried out by a statistician using the R software.

Given the design of the protocol (4 Groups X 3 Time-points), a mixed between-within ANOVA model with Greenhouse-Geisser correction will be used as a statistical test for this purpose. Statistical significance will be set at 0.05 to reject the null hypothesis.

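### The stated 4 x 3 ANOVA treats the T0 score as an outcome level; adjusting for it as a covariate would be more precise at almost no cost

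*Protocol article*

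**What the plan says.** The Outcome measures section of the protocol article states: "Primary outcome measures will be score changes in two functional scales: FIM and UPDRS". The Statistical analysis section opens with "Given the design of the protocol (4 Groups X 3 Time-points" and then names a mixed ANOVA with a Greenhouse-Geisser correction, tested at 0.05. Study design defines the three occasions as T0 (baseline), T1 (four weeks later, at discharge) and T2 (two months after discharge). T0 is therefore one of the three outcome levels, and no covariate is named.

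Demographic and clinical characteristics gives one purpose for baseline age, sex and clinical features: the "clinical characteristics of the subjects will be assessed at T0 (baseline) in all groups to evaluate their homogeneity".

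The Sample size section works "with 80% power and 0.05 alpha in a mixed subjects design (4 groups and 3 time points" and for an effect size of 0.4. It concludes that a "total sample size of 64 participants (16 participants for each group) should be enrolled", and continues: "We plan a sample size of *N* = 80 (*N* for each group = 20" to allow for dropout. It gives neither a dropout rate nor a correlation between time points.

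**The concern.** When baseline is a level of the outcome, the arm-by-time contrast from T0 to a follow-up is a difference in mean change. That subtracts the whole baseline difference between arms, although only the fraction r of it (for equal variances) is expected to persist at follow-up. The excess is noise, and baseline adjustment removes it.

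The group main effect of the same ANOVA has a separate weakness. It averages over all three occasions, including T0, when no arm has been treated.

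What is at stake is precision. The trial has 16 to 20 patients per arm, and its aims include comparing the active arms with each other. The T0 scores are already planned for collection, so the lost precision could be recovered without new data.

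**Working it through.** **The plan's own figure.** The inputs from Sample size are f = 0.4, 80% power, alpha 0.05, four groups and m = 3 time points, with a result of 64. Neither r nor the F test that was powered is stated, so 64 does not follow from these inputs alone. Using the noncentral F distribution:

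- Between-groups test, λ = N f² m / (1 + (m−1)r), df 3 and N−4: N = 52 at r = 0.5, 60 at 0.7, 64 at 0.75 to 0.8, and 68 at 0.9.
- Group-by-time test, λ = N f² m / (1−r), df 6 and 2(N−4): N = 20 at r = 0.5.
- One-way ANOVA, λ = N f²: N = 76.

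Of these, the between-groups test gives 64 if r is about 0.75 to 0.8. The article does not say that this test was used, so r is treated below as an assumption over 0.5 to 0.9.

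**Variance at one follow-up.** Take unit variance at both occasions and correlation r.

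- Change score: 2(1−r).
- Adjusted for T0: 1−r² = (1−r)(1+r).
- Ratio: (1+r)/2.

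With unequal standard deviations s0 (baseline) and s1 (follow-up), the change-score variance exceeds the adjusted variance by s0² + s1² − 2r·s0·s1 − s1²(1−r²) = (s0 − r·s1)². This is never negative, so the direction of the result does not depend on equal variances.

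**Power of a four-arm test at one follow-up, f = 0.4 on the change score.**

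- Change score: λ = N × 0.16, df 3 and N−4. For N = 64, λ = 10.24 and power is 74.2%. For N = 80, λ = 12.80 and power is 84.5%.
- Adjusted: λ = N × 0.16 × 2/(1+r), df 3 and N−5.

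| r | Variance ratio | N matching 64 on change scores | λ, N = 64 | Power, N = 64 | λ, N = 80 | Power, N = 80 |
|---|---|---|---|---|---|---|
| 0.5 | 0.75 | 48 | 13.65 | 86.4% | 17.07 | 93.7% |
| 0.7 | 0.85 | 55 | 12.05 | 81.4% | 15.06 | 90.3% |
| 0.8 | 0.90 | 58 | 11.38 | 79.0% | 14.22 | 88.4% |
| 0.9 | 0.95 | 61 | 10.78 | 76.5% | 13.47 | 86.5% |

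The third column is 64 × (1+r)/2, rounded up.

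**All three occasions.** Assume equal correlations r, unit variances and the same effect τ at T1 and T2. The variance per unit τ² is:

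- Group main effect: the effect shrinks to 2τ/3 and the variance of the three-occasion mean is (1+2r)/3, which gives [(1+2r)/3]/(4/9).
- Mean of T1 and T2 minus T0: (1+r)/2 + 1 − 2r.
- Mean of T1 and T2 adjusted for T0: (1+r)/2 − r².

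| r | Main effect | Change contrast | Adjusted | Adjusted / change | Adjusted / main |
|---|---|---|---|---|---|
| 0.5 | 1.50 | 0.75 | 0.50 | 0.67 | 0.33 |
| 0.7 | 1.80 | 0.45 | 0.36 | 0.80 | 0.20 |
| 0.8 | 1.95 | 0.30 | 0.26 | 0.87 | 0.13 |
| 0.9 | 2.10 | 0.15 | 0.14 | 0.93 | 0.07 |

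**Simulation of the stated model.** There were 4,000 runs with 16 per arm and r = 0.7. Assumed arm effects were 0, τ, τ/2 and τ with τ = 0.65 SD, constant over T1 and T2. Power was 62% for group by time (Greenhouse-Geisser), 23% for the group main effect and 84% for ANCOVA on the T1/T2 mean. With no effect, all three rejected at about 5%. Part of the step from 62% to 84% comes from replacing a 6-df interaction with a 3-df test, so it is not a measure of adjustment alone.

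**The case against.** The strongest reply is that nothing here is an error. Arms are randomised, so the group-by-time test is valid and its change contrasts are unbiased. The article is condensed, and a covariate list is commonly left to an analysis plan. The gain depends on an r that the document does not give, and at r = 0.8 to 0.9 it is only 5 to 10% of variance at one follow-up. The plan is for 80 patients; if all are analysed, the change-score test already has 84.5% power in this setup. The single-follow-up test is also not the planned three-level ANOVA.

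Most of this stands and limits the point to efficiency. It does not remove the point, because the article does more than omit covariates: it names a model in which T0 is an outcome level. Adjusting for T0 means changing that model.

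Several stronger readings are tempting, and the document does not support them:

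- **A significance test of baseline balance that steers the analysis.** The homogeneity sentence mentions no test and no decision that depends on the result. A descriptive baseline table fits its words.
- **Imbalance in Hoehn and Yahr stage carried into the estimates.** Differencing removes any additive effect of stage on score level. Only an effect of stage on change would remain, and the article gives no evidence of one.
- **MIQ-R as a missing covariate.** The article says that "a visual and kinesthetic imagination scale (MIQ-R) will be delivered to each patient enrolled". Its Introduction suggests that the effectiveness of imagery may depend on the ability to imagine. That is possible effect modification, which a covariate main effect would not address. It does not show that MIQ-R predicts FIM or UPDRS.
- **A loss of 74% against 86% under the plan.** That pair holds only at r = 0.5, the most favourable value in the range, with N = 64 and one follow-up.

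**Conclusion.** The point holds as one of lost precision in a stated model. It is not one of bias or inflated type I error. Against the change contrast at a single follow-up, the avoidable variance is 25% at r = 0.5, falling to 5% at r = 0.9. If the effect is equal at T1 and T2 and their mean is analysed, it is 33% falling to 7%. At N = 64 the single-follow-up power gain is between about 12 and 2 percentage points; at N = 80 it is between about 9 and 2. If the group main effect were the test relied on, the loss would be much larger, because the adjusted variance is a third of it or less over this range.

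These sizes rest on assumed correlations, equal variances across occasions and, for power, f = 0.4 placed on the change score. The three-occasion figures also assume equal correlations and a constant effect. The direction of the single-follow-up result needs none of these, apart from the one degree of freedom spent. The gain from stage, age or sex cannot be quantified from the document; the T0 score of the same scale is the main source.

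**What to change.** In Statistical analysis, replace the three-level ANOVA for FIM and UPDRS with a model in which T1 and T2 are the outcomes. This can be an ANCOVA at each follow-up or a repeated-measures model over both. Include the T0 score of the same scale as covariate in every arm contrast, with its slope allowed to differ between T1 and T2 in a joint model.

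The outcome definition can stay as score change: with the T0 score in the model, the arm contrast is the same whether the follow-up score or the change is analysed.

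Hoehn and Yahr stage (II or III) may be added as an optional covariate if it is named in advance. Baseline characteristics can be tabulated by arm as already planned.

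The cost is a change of wording and one error degree of freedom for the T0 score at each follow-up, for example 59 instead of 60 at N = 64. No further data are needed, since FIM and UPDRS are already measured at T0.
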